#### Internet Self-Efficacy Scale

This scale will measure confidence in the ability to use the Internet. Participants rate their confidence on a Likert-type scale and are asked statements such as, “using the Internet to gather data” and “turning to an online discussion group when help is needed” [48].

A complete list of measures and the data collection schedule is provided in Table 1.

**Table 1 Tab1:** Study measures and schedule to acquire data

	Time point		
Measures	Baseline	2 months	6 months
Demographic and clinical variables	X		
Medical Outcomes Study Short Form 36	X		
Self-Efficacy Scale	X	X	X
Change Assessment Scale	X	X	X
Intrinsic Motivation	X	X	X
Apnea Risk Evaluation System Questionnaire	X		
Sleep Hygiene Index	X	X	X
Apnea Knowledge/Apnea Belief Scale	X	X	X
Sleep Apnea Literacy Scale	X	X	X
Test of Functional Health Literacy in Adults (short version)	X	X	X
Internet Self-Efficacy Scale	X	X	X

### Intervention

Participants randomized to the intervention arm will receive an iPad with free access to a password-protected interactive culturally and linguistically tailored sleep informational website. Study assessments will be collected at baseline, 2 months (post-enrollment) and at 6 months (follow-up). Participants will receive a brief 10-minute tutorial by the study team on login procedures and use of the website. Participants will also be able to call the project staff to troubleshoot any issues with the website. Given that this is a web-based intervention, the study setting is the participants’ home.

### Control condition

Participants randomized to the control condition will receive an iPad ﻿with﻿ free access to the NSF and NHLBI website via an iPad. Currently, there is no specific comparative effectiveness data evidencing superiority of any website or other format for increasing sleep health literacy. Furthermore, there has been previous research to suggest the overall difficulty that patients experience in using the NSF materials. Thus, our study will ascertain effectiveness of a tailored website compared to the standard websites. Participants in the control condition will have access to the culturally and linguistically tailored sleep informational website at 6 months post-enrollment date.

## Design and methods: data collection, management, and analysis

Survey data will be collected through a password-protected website, REDCap, a secure website for managing and collecting online survey da﻿ta, which meets the standards set forth by the NYULMC IRB and HIPPA offices. Additional information about data entry, storage, quality and can be found in the IRB study protocol.

### Plans to promote retention

Participants in the intervention arm will be contacted weekly by the PM to ensure ongoing use of the website and access to intervention materials. We will track participant usage based on Google Analytics.

### Sample size

Guided by principles governing the use of focus group data, the sample size will be determined when we reach a point of “saturation”, which is when additional group sessions are not likely to produce new themes. Based on previous research [49, 50], we expect that five groups will be sufficient to capture key themes for the project. In the secondary objective - assuming a medium effect size (d = 0.32), as derived from Cohen [51], and a sample size of 200 - the study will be adequately powered (>85%) to detect significant differences between participants likely to show improvement in health literacy scores and those who are not using Fisher’s exact tests (critical X^2^ = 7.98). In a previous pilot study, we found that 40% of black patients in the community adopted recommendations for OSA treatment after exposure to health messages, which compares to 27% who did without such exposure. Assuming a 13% increase in the likelihood of adoption of health messages and a sample size of 200, the proposed study will have adequate power for a preliminary test of the hypothesis that exposure to health messages will foster improvement in sleep health literacy. Achieving the goal of a 13% increase would have an important public health impact. A two-tailed test, with 85% power and α = 0.05 comparing 27% to 40% requires 100 participants per arm [52].

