### Allocation

Individuals will be eligible for randomization once their baseline questionnaire is completed. Randomization will be carried out in pairs using a table of random permutations conducted by the Program Manager. One member of each pair will be assigned to the Internet-based group and the other to the control group, using sealed envelopes. This strategy ensures equal allocation to the two groups, and that both have similar characteristics regarding measured and unmeasured background variables (i.e., patient characteristics and lifestyle behavior at baseline, medical comorbidities, and situational/contextual factors), which could potentially affect study outcomes. The Program Manager will hold the sequence of assignments and will dispense the code for each new patient upon request by the Research Assistant (RA). If a participant requests to be withdrawn from the study, the Program Manager will assign the code for the next new patient. The Program Manager  will maintain a record of who was randomized to which group to maintain integrity of planned analysis. Due to the nature of the study, the Program Manager will not be blind to the study arms. Randomization will be ongoing until sample size goals are reached: 100 per study arm and in accordance with the CONSORT randomization guidelines as shown in Fig. 2.

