For aim 3, we will examine which subjective measures are associated with increased OSA health literacy using multivariate logistic regressions. The main dependent measure will be a binary factor: [yes versus no]; candidate predictors are indicated in Table 1. We will use multivariate analysis to explore whether sociodemographic variables (e.g., age, income, education), lifestyle practices (e.g., diet, exercise, smoking, and drinking habits), Internet self-efficacy, and baseline sleep measures (e.g., OSA knowledge, OSA beliefs, and knowledge of sleep hygiene) indexing OSA health literacy improved after exposure to health messages. We assess OSA health literacy with the Sleep Apnea Literacy scale, a 24 -item questionnaire developed by a sleep expert, and expert in scale design. The questionnaire assesses sleep apnea knowledge and sleep apnea clinical management. Sample items include “When breathing stops during sleep this is called sleep apnea” and “Loud snoring can be a sign of sleep apnea.” Ninety-one participants average age 38, and 48% white, 27% African American completed the questionnaire. The questionnaire was developed using exploratory and confirmatory analyses. The questionnaire includes items across three scales, including sleep apnea literacy (component alpha 0.74), sleep apnea self-efficacy (component alpha 0.76), and sleep apnea clinical management (component alpha 0.65). The concurrent scale validity is 0.85. To compare participants who exhibited improvement in health literacy and those who did not 2 months post-enrollment, *t* tests and chi-squared tests will be used. Multivariate analysis of covariance will be used to assess effects of sleep health messages on sleep measures (e.g., OSA knowledge, OSA beliefs, knowledge of sleep hygiene, and S-TOFHLA scores); effects of confounders will be adjusted. Baseline subjective factors will be entered in a linear regression model in order to determine which factors are associated with higher health literacy scores. In post hoc analyses, we will also explore whether combined effects of exposure to tailored web-based content, and video vignettes received through the website had greater impact on improvement in sleep apnea literacy scores.

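### The first power statement (d = 0.32, N = 200, power above 85%, critical X² = 7.98) does not follow from its inputs: as labelled, power is about 61%, and 7.98 is not a 0.05 cut-off

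*Protocol article*

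**What the plan says.** The protocol article, Sample size, gives two power calculations for the secondary objective. The first is at issue here. It works "assuming a medium effect size (d = 0.32), as derived from Cohen [51], and a sample size of 200" and concludes that "the study will be adequately powered (>85%) to detect significant differences". The groups it compares are defined by outcome: "differences between participants likely to show improvement in health literacy scores and those who are not". The test is Fisher's exact test, with "critical X^2^ = 7.98" and no degrees of freedom.

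The second calculation, in the same paragraph, compares 27% with 40% using a two-tailed alpha of 0.05 and 85% power, and arrives at 100 per arm. That is the only alpha the paragraph gives. The Allocation section fixes the arm size: "Randomization will be ongoing until sample size goals are reached: 100 per study arm".

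The Statistical analysis section makes the main dependent measure for aim 3 binary. It lists logistic regression, t tests, chi-squared tests and linear regression, and adds: "Multivariate analysis of covariance will be used to assess effects of sleep health messages on sleep measures". Fisher's exact test is not named there.

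**The concern.** The sentence joins parts that do not belong to one calculation. The symbol d normally denotes a standardised mean difference, which is not an input to an exact test on a 2×2 table. An exact test takes its p-value from the table's own conditional distribution, so it has no chi-squared critical value. If d is taken at face value, the stated power is well above what N = 200 delivers. The printed threshold is also far stricter than the usual one for a two-group binary comparison.

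This is one of only two quantitative supports for N = 200 in the randomised comparison. A reader who relies on it would believe the trial adequately powered for an effect of 0.32, and would have no consistent account of the test and significance level behind that belief.

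**Working it through.** **Inputs.** From Sample size: effect 0.32 labelled d, N = 200, stated power above 85%, critical X² = 7.98, and 27% versus 40%. From Allocation: 100 per arm. Two inferences are needed. Two-sided alpha 0.05 is borrowed from the neighbouring calculation. One degree of freedom follows from a binary outcome in two groups.

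**1. Trying to reproduce the power with 0.32 as d, 100 per group.** The expected test statistic is d × √(n/2) = 0.32 × √50 = 2.263.
- Two-sided 0.05: Φ(2.263 − 1.960) = 61.9%. The noncentral t calculation gives 61.5%.
- One-sided 0.05: 73.2% (normal) or 72.9% (t).
- 0.32 read as the arcsine difference h: about 62% by z test; exact Fisher power is 55.6% (27% versus 42.1%) to 57.2% (50% versus 65.7%).

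None of these reaches 85%.

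**2. What 85% would need.** The normal formula is n = 2(1.960 + 1.036)²/d² = 2 × 8.978/0.1024 = 175.4, so 176 per arm; the t calculation gives 176.3, so 177. At 100 per arm the detectable d is (1.960 + 1.036) × √(2/100) = 0.424 (normal) or 0.426 (t), rounded up to 0.43.

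**3. The groups actually named.** The sentence compares improvers with non-improvers, and nothing fixes those at 100 each. The pooled rate of the 27% and 40% scenario is 33.5%, which gives 67 improvers and 133 non-improvers. The expected statistic becomes 0.32 × √(67 × 133/200) = 2.136 and power is 56.6% (t test). Equal groups are the best case, so about 61% is an upper bound for that comparison.

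**4. The critical value.**

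| df | P(χ² > 7.98) | 0.05 cut-off |
|---|---|---|
| 1 | 0.0047 | 3.84 |
| 2 | 0.0185 | 5.99 |
| 3 | 0.0464 | 7.81 |
| 4 | 0.0923 | 9.49 |

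The value 7.98 matches no row. If it were used as a 1 df threshold (√7.98 = 2.825), power for d = 0.32 at 100 per group would be Φ(2.263 − 2.825) = 28.7%.

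**5. The reading that does exceed 85%.** Take 0.32 as the chi-squared effect w, with N = 200. The noncentrality is 200 × 0.32² = 20.48, and its square root is 4.525. Power at 1 df is Φ(4.525 − 1.960) = 99.5% at 3.84, and Φ(4.525 − 2.825) = 95.5% at 7.98.

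For 27% versus 40% with equal arms, w = 0.13/(2√(0.335 × 0.665)) = 0.138, less than half of 0.32. Power for that difference at 100 per arm and two-sided 0.05 is 49.8% for the chi-squared test by full enumeration (49.5% by normal approximation) and 43.5% for Fisher's exact test.

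**The case against.** The strongest objection is that the label, not the power, may be the slip. The sentence quotes a chi-squared critical value, and w is the natural effect index for a chi-squared test. With w = 0.32 the claim of more than 85% is true, even at 7.98. This stands as far as it goes: a reader might infer that the statement is internally impossible, and the document does not support that. It is wrong as labelled. The alternative reading does not rescue it, however. The printed symbol would be wrong, 7.98 would still not be a 0.05 cut-off, and the effect would be more than twice the one implied by the paragraph's own 27% versus 40%. The article does present these as two calculations, so that mismatch shows poor coherence and does not by itself refute the w reading.

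Second, neither the degrees of freedom nor alpha is printed for this sentence. At 3 df, 7.98 gives p = 0.046, close to 0.05. That is correct, and it is why the p = 0.0047 figure must carry its 1 df condition. A two-group binary comparison nevertheless has 1 df, and no other alpha appears in the paragraph.

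Third, a reader might infer that the trial will be tested against 7.98, at roughly a tenth of the intended alpha. Nothing in the Statistical analysis section adopts that threshold, so this consequence is hypothetical.

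Fourth, Fisher's exact test is a close relative of the planned chi-squared tests, so its absence from the Statistical analysis section carries little weight.

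Finally, this sentence takes N = 200 as an input. The 100 per arm is derived from 27% versus 40%, so the more consequential shortfall lies there.

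**Conclusion.** The statement is wrong as written. With d as labelled, 100 per group and two-sided alpha 0.05, power is about 61%, and about 57% at a 67/133 split, against a claim of more than 85%. The printed critical value is not a 0.05 cut-off for any degrees of freedom and has no role in Fisher's exact test. The conclusion rests on three assumptions: that d means a standardised mean difference, that the paragraph's only alpha applies to this sentence, and, for p = 0.0047, that there is 1 df. If 0.32 was meant as w, the power claim holds, but the label and the threshold remain wrong and the effect is out of line with the paragraph's other scenario. Under either reading the text needs correcting. There is also a structural defect: a contrast between improvers and non-improvers is not the randomised contrast, so even a correct figure would not show the trial's power to compare the two websites.

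**What to change.** In Sample size, delete the critical X² of 7.98 and the claim of more than 85%. Replace them with one calculation for the randomised comparison, arm against arm with 100 each, on the binary improvement outcome in the Statistical analysis section. Name the effect index, the test, the degrees of freedom and two-sided alpha 0.05, and state the power obtained. For 27% versus 40% this is about 50% by chi-squared test.

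If a continuous score by arm is also to be powered, say that d = 0.32 gives about 61% unadjusted and that 85% needs d of about 0.43. The article names no by-arm mean comparison of the Sleep Apnea Literacy Scale, so this would be an addition and should be identified as one. Any gain claimed from baseline adjustment should be labelled as resting on an assumed correlation, because the article gives none.

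Make this change together with the correction of the 27% versus 40% claim that sets the arm size. The cost is wording only, with a less favourable stated power.

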**Design and Methods:**

This two-arm randomized controlled trial will assign 200 participants to a culturally and linguistically tailored web-based sleep educational platform. The website will be developed to ensure that the content is user friendly and that it is readable and acceptable by the target community. Participants will receive login information to a password-protected website and will have access to the website for 2 months. Study assessments will be collected at baseline, 2 months (post-enrollment) and at 6 months (follow-up). We will use qualitative and quantitative methods to develop tailored materials and to ascertain whether tailored materials will increase OSA knowledge and OSA health literacy by comparing blacks exposed to tailored materials versus those exposed to standard sleep health literature. We hypothesize that exposure to tailored OSA information will improve OSA health literacy.

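### The 27% versus 40% behind the sample size compares exposure to health messages with no such exposure, but the randomised controls receive the standard sleep websites, and the article does not justify 27% for them

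*Protocol article*

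**What the plan says.** The Sample size section of the protocol article uses pilot data. It reports the following: "40% of black patients in the community adopted recommendations for OSA treatment after exposure to health messages, which compares to 27% who did without such" contact. It carries the difference into the trial ("Assuming a 13% increase in the likelihood of adoption of health messages and a sample size of 200"), describes the trial as a "preliminary test of the hypothesis that exposure to health messages will foster improvement in sleep health literacy", and concludes: "A two-tailed test, with 85% power and α = 0.05 comparing 27% to 40% requires 100 participants per arm".

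The same section also has a separate power statement, based on d = 0.32 taken from Cohen.

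The comparator is described elsewhere. Under Control condition, controls get an iPad with access to the NSF and NHLBI websites, and the stated aim is that "our study will ascertain effectiveness of a tailored website compared to the standard websites". The abstract agrees: the trial works by "comparing blacks exposed to tailored materials versus those exposed to standard sleep health literature". Controls are given the tailored site only at 6 months.

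**The concern.** The power statement needs a rate for the control arm that the trial actually randomises. The article supplies a rate for pilot patients who had not been exposed to health messages. Trial controls are given two sleep-health websites, and nothing in the article links the pilot's 27% to people using them.

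Two things are at stake. First, the 13-point target and the power attached to it may be too favourable for the randomised comparison. Second, because the Sample size section words its hypothesis as exposure to health messages without naming a comparator, a null result could be reported as messages failing to improve literacy. It would show only that no advantage over the standard websites had been demonstrated.

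**Working it through.** **Inputs** (Sample size section): p1 = 0.27, p2 = 0.40, n = 100 per arm, two-sided α = 0.05, stated power 85%. The documents give no rate for users of the NSF and NHLBI websites, so any other control rate below is an assumption.

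**Step 1: the plan's own figure.** With p̄ = (0.27 + 0.40)/2 = 0.335,

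n per arm = [1.960·√(2p̄(1−p̄)) + 1.036·√(p1(1−p1) + p2(1−p2))]² / (p2−p1)²

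= [1.960 × 0.6675 + 1.036 × 0.6611]² / 0.0169 = 235.1, so 236 per arm.

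The stated 100 per arm is not reproduced. Power at 100 per arm is

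Φ{[0.13·√100 − 1.960 × 0.6675] / 0.6611} = Φ(−0.013) = 49.5%.

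Exact enumeration of the two binomials gives 49.8% for the uncorrected chi-squared test and 43.5% for Fisher's exact test. The drop from 85% to about 50% is an arithmetic shortfall in its own right. It does not come from the choice of comparator, but it sets the baseline for Step 2.

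**Step 2: a control arm that gains something from the standard websites.** Assume that the intervention arm stays at 40% and that the standard websites deliver a fraction f of the pilot's 13-point gain. The control rate is then 0.27 + 0.13f. Exact power at 100 per arm, two-sided 0.05:

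| f (assumed) | Control rate | Difference (points) | Chi-squared | Fisher |
|---|---|---|---|---|
| 0 | 27% | 13 | 49.8% | 43.5% |
| 0.25 | 30.25% | 9.75 | 30.3% | 25.0% |
| 0.5 | 33.5% | 6.5 | 15.8% | 12.4% |
| 0.75 | 36.75% | 3.25 | 7.6% | 5.6% |

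Hand check for f = 0.5, with p̄ = 0.3675: Φ{[0.065·√100 − 1.960 × 0.6818] / 0.6803} = Φ(−1.009) = 15.7%, in line with the exact 15.8%.

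**Step 3: what the fixed 200 can detect.** From a 27% control rate, the Step 1 formula at 85% power needs 103.1 (so 104) per arm for 47% and 98.3 (so 99) per arm for 47.5%. About 20.5 points is therefore detectable with 100 per arm. Exact power for chi-squared is 84.0% at 20 points and 85.7% at 20.5. For Fisher it is 83.8% at 21 points and 85.5% at 21.5. The smallest detectable difference is thus about 20 to 21 points by chi-squared and 21 to 22 by Fisher.

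**The case against.** The best defence is that 27% may be a fair control rate. Control condition notes that patients have trouble using NSF materials, and the Background reports that many low-literacy patients needed help reading NSF and AASM brochures. If the standard websites add almost nothing, an unexposed rate is a reasonable stand-in. This could support a low control rate, but the Sample size section does not use it, difficulty is not absence of effect, and the NHLBI site is provided as well. The argument needs to be made in the text.

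A second defence is that the article often uses health messages to mean its own tailored content (hypothesis 3 under Objectives, and Focus groups). This stands. A reader might infer that the trial has two conflicting definitions of its contrast. That goes too far: the abstract and Control condition agree on tailored versus standard, and the Sample size hypothesis can be read as hypothesis 3 shortened. What remains is a planning rate that does not match the comparator, and a hypothesis that does not name one.

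Third, the size of any loss is assumed. No document fixes f or shows that the intervention arm would sit at 40%, and the pilot rates concern adoption of treatment recommendations, whereas the trial outcome is improvement in OSA health literacy. The table in the working is therefore illustrative.

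**Conclusion.** The point holds, within limits. The 13-point difference and the 85% power come from a contrast of exposure with no exposure, and the article does not justify carrying 27% over to controls who use the NSF and NHLBI websites. If those websites have any benefit and the intervention arm stays at 40%, the difference is below 13 points. Power at 100 per arm is then below about 50% (chi-squared) or 43% (Fisher). How far below cannot be derived from the documents.

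Three stronger readings are not supported:

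- **That the pilot comparison group was untreated.** The article says only that these patients lacked that exposure, not what they received.
- **That the trial isolates the effect of tailoring.** Weekly staff contact is described only for the intervention arm (Plans to promote retention), and the video vignettes are part of the intervention (Role model storytelling development). More than tailoring differs between the arms.
- **That the d = 0.32 statement shrinks in the same way.** That value comes from Cohen and is tied to no messages-versus-none contrast, so this point does not affect it.

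**What to change.** In the Sample size section:

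1. Name the hypothesis as the TASHE tailored website programme versus the standard NSF and NHLBI websites.
2. Say that 27% is a no-exposure pilot rate. If it is kept as the control rate, give the reason, for example the reported difficulty with NSF materials.
3. Replace the 85% claim with power at 100 per arm over a range of control rates from 27% upward. Alternatively, state the smallest difference that the fixed 200 can detect with 85% power: about 20 to 21 points by chi-squared, or 21 to 22 by Fisher, from a 27% control rate.
4. State that a null result would mean no demonstrated advantage over the standard websites, not that health messages are ineffective. Do not state that the trial estimates the effect of tailoring alone.

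The cost is a few sentences and one short table, plus a stated power less favourable than 85%. No change in enrolment is needed.

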### Eligibility criteria

Participants must meet the following study criteria: inclusion criteria: self-reported race/ethnicity as African American, African, Caribbean American or black men and women; ages ≥18 years; accessible by telephone; no plans to move away from the region within the year following enrollment; consent to participate, which includes permission to release medical record information; documented OSA risk based on scores received from the Apnea Risk Evaluation System (ARES) questionnaire [42]. Internet access is not an eligibility criterion, as participants will receive an iPad with cellular service.

Exclusion criteria will include: progressive medical illness in which disability or death is expected within 1 year; impaired cognitive or functional ability which would preclude meaningful participation in the study; sleep apnea diagnosis; stated intention to move within the same year of enrollment.

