## Discussion

OSA is one of the most commonly diagnosed sleep disorders that disproportionately affect blacks. With the rapidly changing field of sleep medicine, including the use of home-based sleep studies, patients may require assistance navigating sleep health services [55]. In addition, there are various treatment options, although CPAP is the most effective. Moreover, treatment for OSA is efficacious and can reduce symptoms of co-morbid health conditions including CVD, diabetes, and hypertension. Unfortunately, adherence to treatment for OSA remains suboptimal and blacks in particular may use CPAP far less than their white counterparts, thus limiting their ability to benefit from treatment. Although several factors have been proposed as contributing to poor adherence, including machine difficulties and psychosocial factors, few studies have explored the role of health literacy [19, 55]. Limited health literacy is associated with several health outcomes and requires a complex set of skills. Thus, it is plausible that individuals with limited OSA health literacy would benefit from the intervention, which will utilize a web-based approach to increase OSA health literacy that we are testing.

In conclusion, there is growing interest in using telehealth among minorities [56–58]. Studies are beginning to show that Internet use in minority communities has increased over the last several years. A random-digit telephone survey of New York residents found that 77% had computer access and 65% used the Internet [59]. Online information affects health habits of New York minorities, with 47% in a telephone survey stating it changed their exercise routines and 44%, their eating habits [60]. Computer-based pre-screening is well accepted for HIV testing, with 80% of respondents in one study preferring the computer-based screening compared to other methods [61]. Thus, we believe that an approach that builds on what is now known about the potential role of web-based information might be an effective means to increase OSA knowledge and OSA health literacy, thereby increasing utilization of sleep-related services among blacks.

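### The 13-point goal and its 85% power claim rest on pilot rates of adopting OSA treatment recommendations, an endpoint this literacy trial does not measure

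*Protocol article*

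**What the plan says.** All references are to the protocol article.

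- **Sample size, pilot rates.** "40% of black patients in the community adopted recommendations for OSA treatment after exposure to health messages". The rate given for patients who were not exposed is 27%.
- **Sample size, use of those rates.** The next sentence begins "Assuming a 13% increase in the likelihood of adoption of health messages and a sample size of 200" and ends by claiming adequate power for a preliminary test that health messages improve sleep health literacy. It is followed by "Achieving the goal of a 13% increase would have an important public health impact" and then "A two-tailed test, with 85% power and α = 0.05 comparing 27% to 40% requires 100 participants per arm".
- **Sample size, other power statement.** A little earlier, the section claims more than 85% power for health literacy scores with 200 participants and an effect size of d = 0.32.
- **Objectives and Statistical analysis.** The randomized evaluation concerns OSA health literacy. The main dependent measure for aim 3 is a yes/no factor for increased literacy.
- **Eligibility criteria.** A sleep apnea diagnosis is an exclusion. Entry requires "consent to participate, which includes permission to release medical record information".
- **Measures.** "A complete list of measures and the data collection schedule is provided in Table 1". The table has 11 rows.
- **Discussion.** A web-based approach "might be an effective means to increase OSA knowledge and OSA health literacy, thereby increasing utilization of sleep-related services among blacks". The Abstract makes the same point with the word potentially.

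**The concern.** Within four sentences the Sample size section moves from adopting treatment recommendations, to adopting health messages, to improving health literacy. It treats the same 13 points as if they applied to all three. The first is a health behaviour, seen in people for whom treatment had presumably been recommended. The last is a change in a questionnaire score among people who have no diagnosis. Nothing in the article links a rate on one to a rate on the other.

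Two things are at stake. First, a reader of the final report will want to know whether the declared 13-point goal was met. If the goal means what the pilot rates mean, no scheduled measure can answer that. Second, the stated justification for 100 per arm does not describe the trial's power for the outcome it will analyse, so a null literacy result could be read with unwarranted confidence.

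**Working it through.** **1. Does any measure match the goal?**

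| Element | What the article gives |
|---|---|
| Outcome behind 27% and 40% | Adoption of recommendations for OSA treatment |
| Population behind 27% and 40% | Pilot patients in the community, not described further |
| Trial population | At risk on the ARES questionnaire, no sleep apnea diagnosis |
| Trial outcome (aim 3) | Improvement in OSA health literacy, yes/no |
| Table 1 rows | 11: three at baseline only, eight at baseline, 2 and 6 months |
| Rows recording a sleep consultation, sleep study, diagnosis or treatment start after baseline | 0 |
| Planned analyses of such uptake | None |

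The three baseline-only rows are demographic and clinical variables, the Short Form 36, and ARES. The nearest repeated measures are the Apnea Beliefs Scale, scored as likelihood of adherence, and the Change Assessment Scale, which measures readiness. Neither records whether a recommendation was adopted. The Sleep Hygiene Index does record behaviour at all three visits, but it covers sleep habits and not OSA screening or treatment. The Epworth scale and the website usage metrics are described in the text but are absent from Table 1. They do not record uptake either.

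**2. Does the plan's figure of 100 per arm follow from its inputs?**

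Inputs from Sample size: p1 = 0.27, p2 = 0.40, difference 0.13, two-sided α = 0.05 (z = 1.960), power 85% (z = 1.036). Mean proportion = 0.335.

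n per arm = [z_α √(2 × 0.335 × 0.665) + z_β √(0.27 × 0.73 + 0.40 × 0.60)]² / 0.13²

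= [1.960 × 0.6675 + 1.036 × 0.6611]² / 0.0169 = (1.308 + 0.685)² / 0.0169 ≈ 235.2, so **236 per arm**.

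Other versions of the calculation:

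- unpooled variance: 232
- arcsine: 235
- with continuity correction: 251
- 80% power, two-sided: 206
- one-sided, 85% power: 189

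No two-arm version tried reproduces 100.

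**3. Power with 100 per arm for 27% vs 40%**

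z = (0.13 × √100 − 1.308) / 0.6611 = −0.0125, so power = **49.5%** (43% with Fisher's exact test, the test named in the section).

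**4. The other power statement**

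Read as a standardized mean difference, d = 0.32 with 100 per arm gives z = 0.32 × √50 − 1.960 = 0.303, or about 62% power. Power of 85% would need 176 per arm. If 0.32 was instead meant as the chi-squared effect size w, power with 200 participants is about 99%. Neither reading is tied to an expected proportion improving on the Sleep Apnea Literacy Scale.

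**5. What 100 per arm can detect on a binary literacy endpoint**

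The article gives no expected improvement rates, so I assume a mean proportion p between 0.3 and 0.7. The detectable difference at 85% power is roughly (1.960 + 1.036) × √(2p(1 − p)/100). For p = 0.3 or 0.7 this is 2.996 × 0.0648 = 19 points. For p = 0.5 it is 2.996 × 0.0707 = 21 points.

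**6. Precision if uptake were recorded**

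At 27% and 40% with 100 per arm, the 95% half-width of the difference is 1.960 × √(0.4371/100) = 1.960 × 0.0661 = 0.130, about ±13 points.

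**The case against.** The best defence is that the randomized comparison is stated throughout as OSA health literacy, and Table 1 schedules the Sleep Apnea Literacy Scale at baseline, 2 and 6 months. The goal sentence says only a 13% increase, without naming the outcome. Read as 13 points more participants with improved literacy, the goal can be measured. This stands, and it means the trial does have an assessable objective. It does not rescue the Sample size section, because on that reading 27% and 40% are not rates for the endpoint and the basis for the assumption disappears.

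It is also fair that use of sleep services is a hedged hope in the Abstract and Discussion and not a declared endpoint. A trial need not measure every downstream benefit. An article may also condense a fuller protocol, but this one calls its list of measures complete, and its analysis section names no uptake outcome.

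A reader might go further and infer that the trial collects only test scores. The Sleep Hygiene Index, repeated at both follow-ups, shows otherwise. A reader might also infer that participants diagnosed during follow-up would be taught in clinic and that this would distort the 6-month comparison. The documents give no diagnosis rate and no evidence that such teaching changes these scores. Diagnosis prompted by the website would be part of its effect, and diagnosis unrelated to it is expected equally in both randomized arms.

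**Conclusion.** The point holds as a mismatch inside the Sample size section. The 13-point goal and the 85% power claim come from an outcome that none of the 11 Table 1 rows records and no planned analysis uses. They also appear to come from a different population. That last part is an inference: the article does not say whether the pilot patients were diagnosed, only that they adopted treatment recommendations, whereas the trial excludes anyone diagnosed. The claim is also numerically wrong for its own contrast, with about 50% power at 100 per arm and about 236 per arm needed for 85%.

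The documents do not support the wider inference that the trial cannot be judged. The literacy comparison remains measurable and randomized. What remains unknown is its power, because no literacy improvement rates are given. The 19 to 21 points above rest on my assumed range of improvement rates.

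**What to change.** **Needed, in Sample size:**

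1. State that 27% and 40% come from a different outcome and population.
2. Stop presenting the 13-point rise as this trial's goal.
3. Base the power statement on the literacy-improvement endpoint: give the assumed proportion improving in each arm and its source, and report the power that 100 per arm provides.
4. Remove the claim that 27% vs 40% needs 100 per arm at 85% power.

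This costs a few sentences and a short recalculation. If the recalculated power is low, the section should say so plainly or the sample size should be revisited.

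**Optional:** add a few self-reported REDCap items at 2 and 6 months in both arms, covering sleep consultation, sleep study, diagnosis and treatment start. Report the between-arm difference as an exploratory estimate with its 95% interval (about ±13 points at the pilot rates), not as a powered test. The 27% vs 40% contrast should not be carried over as a target for these items, since the population differs and power would be about 50%. The cost is a few questions at existing visits, with the usual limits of self-report.

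**If the items are not added:** confine conclusions to literacy and make no claim about use of sleep services.
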